## Methods/Design

### Study design

A 16-week parallel, double-blind, randomized, placebo-controlled dietary supplementation trial will be conducted in the Respiratory Medicine department at the Repatriation General Hospital (RGH), Adelaide, South Australia in collaboration with the Nutritional Physiology Research Centre (NPRC), University of South Australia, Adelaide, South Australia and the Clinical Nutrition Research Centre, University of Newcastle, Callaghan, NSW. Participants will attend the RGH on two occasions (pre- and post-intervention) for a series of tests including pulmonary function, venepuncture, well-being questionnaires and functional exercise capacity (see Figure 1).

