### Sample Size

As this is a feasibility study designed to determine pragmatic aspects of methodology, formal sample size calculations are not appropriate [26,29]. The target sample size for the feasibility study is 40 participants. The target sample is to allow sufficient precision to enable sample size calculations for subsequent studies. Browne [30] suggests that a minimum of 30 participants is required to achieve sufficient precision, a recommendation supported by Lancaster *et al*. [31]. The target sample of 40 enrolled participants will allow completion of 30 subjects, allowing for a 25% participant dropout rate. A key feasibility criterion is the ability to recruit a target sample of 40 participants within 52 weeks.

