### Randomization

Subjects will be randomly allocated by minimization [32,33], based on modified Medical Research Council (mMRC) scale for breathlessness scores, to either the fish oil group or the placebo group. The prognostic factor that will be considered in the minimization model will be mMRC score (0, 1, 2, 3 or 4).

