#### Functional exercise capacity

The six-minute walk test will be used to determine change in functional exercise capacity (six-minute walk distance). Participants walk on a hard flat surface as far as they can in six minutes (one lap up and back = 40m), stopping for breaks if required. The test will be conducted twice with the maximum walk distance used for analysis. The six-minute walk test is a reliable (CV = 8%, intra-class correlation coefficient = 0.93) measure when conducted under standardized conditions [53,54] and is commonly used as an indicator of functional exercise capacity in the COPD population [55-57] as well as other chronic diseases such as cardiovascular disease [58].

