### Data analysis

SPSS version 17 for WINDOWS [International Business Machines Corporation (IBM), New York, USA] will be used for analyses. Data will be cleaned, checking for errors or missing values. Continuous data will be checked for normality of distribution and non-normally distributed data will be transformed where possible. Scatter plots will be used to determine nature/shape of relationships before applying linear regression.

The primary focus of this study is feasibility, which will be analyzed using descriptive statistics and frequency tables. The key feasibility outcomes are:

1. Recruit 40 participants in 52 weeks;

2. Complete the intervention in 75% of all recruited participants;

3. ≥2% change in total erythrocyte LCn-3PUFA and ≥80% of capsules consumed (estimated from remaining capsules);

4. A positive moderate effect size (≥0.2) in at least three scientific outcome measures (between active and placebo groups).

Analysis of variance (ANOVA) with repeated measures will be used to estimate the effect size of LCn-3PUFA versus placebo supplementation on the scientific outcome measures (six-minute walk, pulmonary function tests, questionnaire scores, blood biomarkers of inflammation and symptoms (for example, high sensitivity C-reactive protein, dyspnea and impulse oscillometry)). Progressive Bonferroni corrections will be used to correct for the effects of multiple outcomes. Comorbid status and severity of exacerbations will be assessed as potential confounders using multiple regression analysis.

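### With one pre and one post visit, repeated-measures ANOVA estimates the treatment effect less precisely than baseline-adjusted ANCOVA for outcomes with low to moderate pre-post correlation

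*Protocol article*

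**What the plan says.** The method for the scientific outcomes is fixed in one sentence of the protocol article (Data analysis): "Analysis of variance (ANOVA) with repeated measures will be used to estimate the effect size of LCn-3PUFA versus placebo supplementation". The outcomes listed there are the six-minute walk, pulmonary function, questionnaire scores and blood markers. Table 1 also enters ANOVA as the statistical test for the proposed study.

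The Study design section sets the number of measurements: "Participants will attend the RGH on two occasions (pre- and post-intervention) for a series of tests".

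Two statements show what the estimates are for. The fourth key feasibility outcome under Data analysis requires "A positive moderate effect size (≥0.2) in at least three scientific outcome measures (between active and placebo groups". The Sample Size section gives the reason for the number enrolled: "The target sample is to allow sufficient precision to enable sample size calculations for subsequent studies".

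On covariates, Data analysis names only two, in a separate model: "Comorbid status and severity of exacerbations will be assessed as potential confounders using multiple regression analysis". The baseline value of the outcome is not mentioned.

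**The concern.** With two time points, the group-by-time term of a repeated-measures ANOVA is the two-sample t-test on change scores. Subtracting the baseline in full is the best use of it only when baseline and follow-up are almost perfectly correlated. At lower correlations the subtraction adds the noise of the baseline measurement to the outcome. ANCOVA instead estimates how much of the baseline to subtract, and in large samples its variance is lower for any correlation below 1.

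At stake is the precision of the treatment-effect estimates from about 30 completers. Those estimates decide the effect-size criterion and will be carried into planning a larger trial. The baseline values are collected in any case, so avoidable width in these intervals is a loss with little to set against it.

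**Working it through.** **The plan's own figure.** The Sample Size section says "The target sample of 40 enrolled participants will allow completion of 30 subjects, allowing for a 25% participant dropout rate". Check: 30 / (1 − 0.25) = 40, which agrees. The article states no power or interval width for the ANOVA, so there is no further figure to reproduce.

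**Inputs.** From the article: two visits and 30 completers. Assumed: 1:1 allocation, hence n = 15 completers per arm; the same SD σ at both visits; random dropout; two-sided 95% intervals; and a pre-post correlation ρ between 0.3 and 0.93. The upper end comes from Functional exercise capacity: "The six-minute walk test is a reliable (CV = 8%, intra-class correlation coefficient = 0.93) measure when conducted under standardized conditions". That is a test-retest coefficient, so it is an upper guide to the correlation over 16 weeks.

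**Variances of the treatment difference.**

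- Change scores (group-by-time): 2σ²(1 − ρ) × (2/n)
- ANCOVA: σ²(1 − ρ²) × (2/n)
- Ratio, ANCOVA to change: (1 − ρ)(1 + ρ) / [2(1 − ρ)] = (1 + ρ)/2

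**Half-widths at n = 15.** The change-score interval uses a t quantile on 28 df. The ANCOVA interval uses 27 df, and its variance is multiplied by 1 + 1/(30 − 4) = 1.038 for estimating the slope. At ρ = 0.5, with σ = 1:

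- Change: √(2 × 0.5 × 2/15) = 0.365; times 2.048 = 0.748
- ANCOVA: √(0.75 × 2/15 × 1.038) = 0.322; times 2.052 = 0.661

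| ρ (assumed) | Large-sample variance ratio | Half-width, change (SD) | Half-width, ANCOVA (SD) | ANCOVA / change |
|---|---|---|---|---|
| 0.3 | 0.650 | 0.885 | 0.728 | 0.823 |
| 0.5 | 0.750 | 0.748 | 0.661 | 0.884 |
| 0.7 | 0.850 | 0.579 | 0.545 | 0.941 |
| 0.8 | 0.900 | 0.473 | 0.458 | 0.968 |
| 0.93 | 0.965 | 0.280 | 0.281 | 1.003 |

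**Adding the minimization factor.** Simulations used 3,000 trials per scenario: 40 participants minimized on a five-level mMRC score, 30 random completers, ρ of 0.5, 0.7 and 0.93, mMRC-baseline correlation of 0.3 or 0.5, and a partial mMRC effect of 0 to 0.2, all assumed. Relative to ANCOVA with baseline only, a linear mMRC term changed the mean half-width by about −3% to +1%. A categorical term widened it by about 0.5% to 5%. Coverage was 0.94 to 0.96 for every model, including those without mMRC.

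**The case against.** The main objection is that this is a preference about efficiency in a study whose primary focus is feasibility, analysed descriptively. Under randomization the change-score contrast is unbiased, no stated figure is wrong, and enrolment stays at 40. All of that stands and limits the weight of the point. It does not remove it, because the method is stated rather than left open, and its output feeds one of the four key feasibility outcomes.

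Several stronger readings are tempting, and the article does not support them.

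- **That leaving out mMRC is a flaw.** Randomization says "The prognostic factor that will be considered in the minimization model will be mMRC score (0, 1, 2, 3 or 4", and Data analysis does not mention the score. A condensed article that is silent on a covariate has not excluded it. The simulations also show little effect on precision and no visible harm to coverage.
- **That the gain is free for every outcome.** At ρ near 0.93 the lost degree of freedom cancels it. The article gives no correlations for CRP or the cytokines, so a claim that they gain most would be a guess.
- **That ANCOVA makes 30 completers worth 40 and so recovers the dropout allowance.** In large samples 30 / 0.75 = 40 at ρ = 0.5, but only for the mean difference. The sample size is justified by precision for later sample size calculations. The relative precision of an SD is about 1/√(2 × df), whatever ρ is: 13.4% on 28 df and 13.9% on 26 df, so marginally worse with two covariates.
- **That variance information for planning is lost.** Table 2 lists the SDs of the outcomes as a separate item. With pre, post and change SDs, the correlation and the baseline-adjusted SD can be recovered.
- **That the effect would be halved.** The group main effect averages both visits and would halve it, but the article does not say it will use that term. Group-by-time is the natural reading.

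**Conclusion.** The point holds as a modest, outcome-dependent loss of precision. Under the stated assumptions, repeated-measures ANOVA gives intervals that ANCOVA would shorten by about 18% at ρ = 0.3, 12% at 0.5, 6% at 0.7 and 3% at 0.8, with nothing gained near 0.93. It is not a bias or an arithmetic error. Nearly all the gain comes from the baseline value rather than from mMRC.

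Nor would the change make the effect-size criterion secure. At ρ = 0.5 the ANCOVA half-width of 0.661 SD is still more than three times the 0.2 threshold (0.661 / 0.2 = 3.3), and the effect on the decision itself has not been quantified. The size of the gain rests on assumed correlations, equal variances at the two visits and 15 completers per arm. Its direction at low to moderate correlation does not depend on the exact value of ρ.

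**What to change.** Replace the ANOVA sentence in Data analysis with wording such as: *For each continuous scientific outcome, the week-16 value will be analysed by ANCOVA with arm and the baseline value of that outcome. The adjusted difference with its 95% confidence interval, the residual SD and the pre-post correlation will be reported.* Base the fourth key feasibility outcome on this adjusted difference, and name the SD by which it is divided.

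Optionally, add mMRC as one linear term, except where mMRC is itself the outcome and would enter twice. Little change in precision should be expected from it. The existing provision for transforming non-normal data can stay as it is.

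The cost is one degree of freedom for the baseline value and a second if mMRC is added, so 27 or 26 in place of 28 with 30 completers. No additional data are needed, and the article's Trial status says recruitment had not begun.

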## Background

Chronic obstructive pulmonary disease (COPD) is a progressive lung disease characterized by irreversible airway obstruction and systemic inflammation [1]. In 2008, COPD was the fourth leading cause of death worldwide [2], and is predicted to be the third leading cause of death by 2030 [3]. Airway obstruction is caused by inflammation of the bronchi leading to increased mucus secretion (chronic bronchitis) and destruction of lung parenchyma leading to distal airway dynamic compression (emphysema). Air flow is further limited by structural changes that occur as a result of chronic inflammation [1]. The clinical signs and symptoms of COPD include dyspnea, productive cough, wheeze, fatigue, reduced exercise tolerance and repeated respiratory infections. Exacerbations (acute worsening of symptoms leading to a change in medication or management) caused by infection, change of season and air pollution, commonly occur in people with COPD and contribute to the overall severity of the disease [1]. The perception of breathing discomfort known as dyspnea, is one of the most common life impairing symptoms of COPD [4]. Dyspnea restricts and reduces physical activity in people with COPD, which over time leads to a more sedentary lifestyle, reduces cardiorespiratory fitness and quality of life [4].

In people with COPD, both airway and systemic inflammation occur. It is unclear whether systemic inflammation is pathological or results from an overflow of inflammatory mediators from the lung [5]. Nonetheless, the systemic inflammation associated with COPD can impair skeletal muscle function and mass, cardiovascular function, skeletal integrity and mental health, and therefore increase the risk of diseases such as osteoporosis, cardiovascular disease, diabetes and depression [5-8]. Dietary interventions which have been shown to be beneficial in the treatment of inflammatory diseases such as rheumatoid arthritis and cardiovascular disease, such as supplementation with long-chain omega-3 polyunsaturated fatty acids (LCn-3PUFA), might also be beneficial for people with COPD.

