Excluding the current protocol, the search of the clinical trials registries identified two randomized controlled trials currently underway (University of Columbia [20] and Texas A&M University [21]). The University of Columbia study is a pilot randomized controlled trial with a lower dose of LCn-3PUFA (2.5 g/day DHA + EPA) than the proposed study, but for a longer supplementation period. The Texas A&M University randomized controlled trial has a similar dose to the proposed study (3.5 g/day DHA + EPA) but for a shorter supplementation period (8 weeks). There are similarities between the three studies (for example, outcomes and omega-3 dose) although the primary focus of the three proposed studies differs, with Columbia University focusing on endothelial function, Texas A&M focusing on muscle repair and damage, while the proposed study focuses on feasibility for a larger RCT.

In theory, LCn-3PUFA from fish oil may improve efficacy of current treatments for COPD by reducing inflammation. Given the paucity of data for fish oil supplementation trials in people with COPD, there are currently no data to guide study design decisions such as appropriate outcome measures (including the primary outcome), likely effect sizes or sample size determination. COPD is a complex condition where comorbidities and exacerbations are to be expected, both of which may confound the effect of, or adherence to supplementation. In addition, slow recruitment and high dropout rates have been reported in intervention trials for people with COPD [22-24]. The driver for this proposed research is the hypothesis that LCn-3PUFA supplementation as an adjunct therapy will improve health outcomes in people with COPD. However before this hypothesis can be tested, it is important to establish the feasibility of the study protocol and justification for continuing to a larger study.

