#### Process outcome measures

A number of process outcomes will be assessed throughout the study including participant recruitment and retention, supplement adherence, time lost to exacerbation and participant experiences and perspectives about participating in the study. Participant recruitment and retention will be assessed descriptively by recruitment and refusal rates, while retention will be determined by the number of enrolled participants who complete the study protocol.

Supplement adherence will be assessed in three ways. Firstly, by determining changes from baseline to post-intervention in the LCn-3PUFA content of erythrocytes, as the LCn-3PUFAs are incorporated into erythrocyte membranes in a dose-dependent and time-dependent manner [41]. Secondly, a symptom diary will be used to document self-reported supplementation consumption including whether the capsules were consumed each day, how many capsules were consumed and whether any side effects were experienced such as eructation or heartburn. Thirdly, participants will be asked to return all unused capsules at the completion of the study and the remaining capsules will be counted.

The time lost to exacerbation (change in usual symptoms potentially leading to a change in medication, change in usual activities or unscheduled visit to a doctor) will be determined using a symptom diary in the format of one month per page. The diary enables the assessment of exacerbation frequency and severity during the supplementation period. The number of exacerbation days will be counted from the diary, while an exacerbation severity score will be calculated using methods adapted from those described by Effing *et al*. [42]. Data collected from the symptom diary will be used to determine the frequency of exacerbation, whether periods of exacerbation impact upon supplement consumption and whether periods of exacerbation have a confounding effect on supplementation or study outcomes. This information will be used to determine whether exacerbations during the supplementation period should be an exclusion criterion in a subsequent study.

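### Exacerbation severity recorded during supplementation is labelled a potential confounder, but it arises after randomization, cannot confound the randomized comparison, and should stay out of any treatment-effect model

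*Protocol article*

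**What the plan says.** The Data analysis section of the protocol article makes two statements that bear on this point. The effect size has its own method: "Analysis of variance (ANOVA) with repeated measures will be used to estimate the effect size of LCn-3PUFA versus placebo supplementation". No covariate is named there. The last sentence of the section adds: "Comorbid status and severity of exacerbations will be assessed as potential confounders using multiple regression analysis".

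The Process outcome measures section shows where the severity variable comes from. "The diary enables the assessment of exacerbation frequency and severity during the supplementation period"; exacerbation days are counted from it, and "an exacerbation severity score will be calculated using methods adapted from those described by" a cited earlier study. One declared use of the diary data is to find out "whether periods of exacerbation have a confounding effect on supplementation or study outcomes". Another concerns the next trial: "This information will be used to determine whether exacerbations during the supplementation period should be an exclusion criterion in a subsequent study".

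The article describes no measure of exacerbation severity before randomization. Comorbid status, the other variable in the regression, comes from two indices described under Comorbid status, where the time of measurement is not stated.

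**The concern.** A confounder of a treatment comparison is a common cause of treatment and outcome. Allocation here is by minimization on the mMRC score, so nothing that happens during the 16 weeks of supplementation can be a cause of allocation. On-study exacerbation severity is therefore not a confounder of fish oil versus placebo.

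It may instead be a consequence of treatment. The Background gives the rationale that "LCn-3PUFA from fish oil may improve efficacy of current treatments for COPD by reducing inflammation", and it describes the event itself in symptom terms: "Exacerbations (acute worsening of symptoms leading to a change in medication or management". Milder exacerbations could be one route by which fish oil improves dyspnea or quality of life. Adjusting for severity would then remove that route from the estimate. If severity and outcome also share unmeasured causes, such as underlying disease activity, adjustment adds a further bias.

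At stake is the between-arm effect size. Key feasibility outcome 4 asks for ≥0.2 in at least three scientific outcomes, and the study is meant to inform the design of a larger trial.

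**Working it through.** **Step 1: can severity be read as a baseline variable?** No. The diary covers the supplementation period, the score is computed from it, and no pre-randomization severity measure is described.

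**Step 2: the plan's own figure.** The Sample Size section enrols 40 to obtain 30 completers with 25% dropout: 30 / (1 − 0.25) = 40. This reproduces. An even split, which is an assumption, gives 15 completers per arm.

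**Step 3: what adjustment estimates.** Let severity and outcome each have within-arm SD 1, with a higher outcome better. The article names no effect-size metric, so I take a standardized mean difference. Let
- τ = total treatment effect on the outcome
- a = effect of treatment on severity (negative if fish oil lowers it)
- b = effect of severity on the outcome (negative if worse severity harms it)
- c = severity–outcome association from shared unmeasured causes

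The within-arm slope of outcome on severity is b + c, and the arms differ in mean severity by a. The treatment coefficient adjusted for severity is therefore

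τ − a × (b + c).

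**Step 4: illustration with τ = 0.2.** The documents give no values for a, b or c, so all are assumed.

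| a | b | c | Adjusted effect |
|---|---|---|---|
| 0 | any | any | 0.20 |
| −0.1 | −0.3 | 0 | 0.2 − 0.03 = 0.17 |
| −0.3 | 0 | −0.09 | 0.2 − 0.027 = 0.173 |
| −0.3 | −0.3 | 0 | 0.2 − 0.09 = 0.11 |
| −0.3 | −0.3 | −0.09 | 0.2 − 0.117 = 0.083 |
| −0.5 | −0.3 | −0.09 | 0.2 − 0.195 = 0.005 |

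The first row shows no bias when treatment leaves severity unchanged. The third shows that bias remains even if severity has no effect of its own on the outcome, provided treatment changes severity and the two share causes.

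**Step 5: simulation check.** With 15 per arm and 20,000 runs, the last two rows gave mean adjusted effects of 0.082 and 0.006. The chance that one outcome's estimate reaches 0.2 was about 50% unadjusted. Adjusted, it was 37% (a = −0.3) and 29% (a = −0.5).

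**Step 6: scale.** The standard error of an effect size of 0.2 with 15 per arm is √(2/15 + 0.2²/60) = √0.134 ≈ 0.37. The between-arm difference in severity is known about as imprecisely: √(2/15) ≈ 0.365, or a 95% half-width of 1.96 × 0.365 ≈ 0.72 SD. The trial's own data could not establish that a is zero.

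**The case against.** The strongest reply is that the effect size does not come from this regression. The Data analysis section assigns it to repeated-measures ANOVA, key feasibility outcome 4 is a contrast between the arms, and Table 2 takes the variance estimate from the outcomes' standard deviations rather than from regression residuals. A reader might infer that the adjusted coefficient will decide whether the study meets its criterion or will set the next sample size. The documents do not say so. This part of the reply stands. What remains is that a variable is usually assessed as a confounder in order to decide whether to adjust for it, and nothing in the text rules out using the adjusted figure.

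Second, asking how exacerbations relate to adherence and outcomes is a fair question for a feasibility study. The Discussion explains that exacerbations may disrupt supplement intake, and time lost to exacerbation is already a process outcome in Table 2. This also stands. The objection is to the confounder label and to adjusting the treatment contrast, not to studying exacerbations.

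Third, the sizes are assumed, can be zero, and in all the examples are smaller than the standard error of about 0.37. That is right, and it means no figure for the bias can be claimed.

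Fourth, a reader might infer that the next trial will drop people who exacerbate after randomization. The article only poses this as a question for a later study and adopts no such exclusion. The question is still badly framed, because on-study exacerbation is an event that treatment may affect.

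Finally, this is a condensed article, and model details may sit elsewhere. That would excuse a missing model specification. It does not excuse a stated classification of a post-randomization variable as a confounder.

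**Conclusion.** The point holds in a limited form. The article states a wrong classification: on-study exacerbation severity cannot confound the randomized comparison, and a treatment effect adjusted for it can be biased as an estimate of the total effect. The bias is zero if treatment does not change severity. Otherwise its size and direction depend on quantities the documents do not give. In the illustrations, a true 0.2 becomes anything from 0.20 to 0.005.

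The ≥0.2 criterion and later planning are affected only if the regression-adjusted figure replaces or modifies the ANOVA estimate, and the text leaves that open. It would go too far to say that the effect size the trial delivers is biased as planned. The objection does not extend to comorbid status if it is taken at baseline. The illustrations rest on a linear model, a standardized mean difference, and an even split of 30 completers.

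**What to change.** In the Data analysis section:
- State that the effect size used for key feasibility outcome 4 and for later planning excludes on-study exacerbation severity.
- Restrict covariates in any treatment-effect model to baseline variables, for example the outcome's baseline value, baseline mMRC (the minimization factor) and a comorbidity index taken at baseline.
- Report exacerbation days and severity by arm as an outcome. The diary already supplies both, so only the split by arm is new.
- Label the regression relating exacerbations to adherence and outcomes as exploratory, and drop the word confounder for on-study severity.

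In the Process outcome measures section, reword the sentence about a subsequent study so that these data are not used to justify excluding randomized participants for exacerbations on study. Use them instead to set that trial's dropout allowance and to pre-specify how exacerbations are handled in its analysis.

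The cost is a few sentences. No new data are needed, and the target of 40 enrolled and 30 completers does not change.

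### Exacerbation severity scored during supplementation is treated as a potential confounder, but it arises after randomization and may be a mediator of the fish oil effect

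*Protocol article*

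**What the plan says.** The Data analysis section of the protocol article contains two separate statements. Repeated-measures ANOVA "will be used to estimate the effect size of LCn-3PUFA versus placebo supplementation on the scientific outcome measures"; no covariates are named, and Table 1 also lists ANOVA as this study's test. The same paragraph then adds that "Comorbid status and severity of exacerbations will be assessed as potential confounders using multiple regression analysis".

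The section on process outcome measures shows where the severity variable comes from:

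- An exacerbation is a "change in usual symptoms potentially leading to a change in medication, change in usual activities or unscheduled visit to a doctor".
- "The diary enables the assessment of exacerbation frequency and severity during the supplementation period".
- From the diary, "an exacerbation severity score will be calculated using methods adapted from those described by" a cited earlier study.
- The diary data are also to show "whether periods of exacerbation have a confounding effect on supplementation or study outcomes".
- The use to be made of this is stated: "This information will be used to determine whether exacerbations during the supplementation period should be an exclusion criterion in a subsequent study".

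The Background gives the rationale that "LCn-3PUFA from fish oil may improve efficacy of current treatments for COPD by reducing inflammation". It states no expected effect of fish oil on exacerbations.

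**The concern.** A confounder of a treatment comparison is a common cause of treatment and outcome. Allocation here is fixed before the first diary entry, so nothing recorded in the diary can have influenced it. Exacerbation severity during supplementation is either unaffected by treatment, in which case it is merely prognostic, or affected by it, in which case it is an intermediate variable. On the trial's own anti-inflammatory rationale the second is plausible.

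The variable also overlaps the outcomes. An exacerbation is defined partly by changed symptoms, and resting dyspnea is rated as an average over the previous two weeks. Adjusting for an exacerbation late in follow-up would partly adjust for the outcome itself.

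Two things are at stake. If the regression makes the arm difference shrink, the natural reading under the planned label is that exacerbations confounded the effect, when the treatment may have worked through them. The result is also meant to inform whether exacerbations become an exclusion criterion in the next study, so the misreading would carry into that design.

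**Working it through.** **The plan's own figure.** The protocol gives no figure for the exacerbation adjustment. The only related figure is the sample size: 30 completers with 25% dropout gives 30 / (1 − 0.25) = 40, as stated. The check below uses 30 completers, 15 per arm.

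**Model.** Let T be the arm (1 = fish oil), M exacerbation severity in SD units, U an unmeasured common cause such as frailty, and Y an outcome in SD units with higher values better.

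- M = aT + hU + error
- Y = dT + bM + gU + error

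Here a is the effect of fish oil on severity, b the effect of severity on the outcome, d the direct effect of fish oil, and h and g the loadings of U on severity and outcome.

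- Regression on arm alone estimates the total effect, **d + ab**.
- Given T and M, the expected value of U is h(M − aT). Regression on arm and severity therefore gives the arm coefficient **d − agh**.

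**Inputs.** The documents give none of a, b, d, g or h; all are assumptions. The 0.2 threshold comes from key feasibility outcome 4 and is read here as a standardized mean difference.

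| Scenario | a | b | d | h | g | Total: d + ab | Adjusted: d − agh |
|---|---|---|---|---|---|---|---|
| A: no effect on severity | 0 | −0.4 | 0.3 | 0.5 | −0.4 | 0.3 + 0 = 0.30 | 0.3 − 0 = 0.30 |
| B: small effect, no U | −0.25 | −0.4 | 0.2 | 0 | 0 | 0.2 + 0.10 = 0.30 | 0.20 |
| C: larger effect, no U | −0.5 | −0.4 | 0.1 | 0 | 0 | 0.1 + 0.20 = 0.30 | 0.10 |
| D: as C, with U | −0.5 | −0.4 | 0.1 | 0.5 | −0.4 | 0.1 + 0.20 = 0.30 | 0.1 − 0.10 = 0.00 |
| E: fully mediated, with U | −0.5 | −0.4 | 0 | 0.5 | −0.4 | 0 + 0.20 = 0.20 | 0 − 0.10 = −0.10 |

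Large-sample simulation agreed with these formulas to within 0.005.

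**At 30 completers** (20,000 simulated trials per scenario), the chance that a single outcome's estimate reaches 0.2 was:

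| Scenario | Without severity | With severity |
|---|---|---|
| A | 0.61 | 0.64 |
| B | 0.62 | 0.50 |
| C | 0.60 | 0.39 |
| D | 0.61 | 0.26 |
| E | 0.50 | 0.16 |

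In A the adjustment does no harm and slightly improves precision (SD of the estimate 0.364 without severity, 0.297 with it). In B to E it moves the estimate away from the total effect. These chances show what would follow if the adjusted estimate were used; the protocol does not say that it will be.

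**The case against.** The strongest reply is that the planned effect sizes are untouched. The text says that severity will be assessed as a potential confounder, not that it will be adjusted out, and the effect sizes are assigned to an ANOVA without named covariates. A reader might infer that severity is to be regressed out of the treatment effect that decides key outcome 4. The document does not say so, and on its plain reading that outcome rests on the unadjusted comparison. This part of the reply stands.

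Second, the stated purpose is largely a feasibility question: whether exacerbations disturb capsule intake and the pre/post measurements. Relating severity to adherence and outcomes as exploration is reasonable. That also stands, but it does not make the variable a confounder of the randomized comparison.

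Third, the bias is conditional. A reader might infer that any adjusted estimate is biased and may change sign. Scenario A shows no bias when fish oil leaves severity unchanged. With a direct effect that is zero or beneficial, reversal needs both a strong mediated path and an unmeasured common cause, as in E. The Background describes direct cellular actions of EPA and DHA, so full mediation through exacerbations is an extreme case, least plausible for a blood marker such as CRP.

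What remains is that the protocol does not say which estimate stands if the regression appears to show confounding, and that it gives the exacerbation result a decision of its own.

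**Conclusion.** The point holds in a limited form. Severity of exacerbations during supplementation is a post-randomization variable. Calling it a potential confounder is wrong, and a treatment effect adjusted for it would not be the total effect of fish oil versus placebo if fish oil alters severity. The general consequence is attenuation: 0.30 to 0.20 or 0.10 for assumed effects on severity of −0.25 or −0.5 SD without a common cause, and to 0.00 when a common cause is added. The range includes no change at all. The documents give no basis for choosing among these values.

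The threat to key outcome 4 and to the next trial's effect sizes is indirect, through displacement or reinterpretation of the ANOVA result. The threat to the decision about exacerbations in a later study is more direct. In a 40-person feasibility study whose primary analysis is descriptive, this should be corrected, but it does not undermine the design.

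**What to change.** In the Data analysis section:

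- Remove severity of exacerbations from the confounder regression. Limit adjustment to variables fixed before randomization: the baseline value of the outcome, the mMRC score used in minimization, and comorbid status measured at baseline.
- State that the effect sizes for key outcome 4 and for planning the next trial are those without on-treatment exacerbation severity.
- Label any model that contains exacerbation severity as exploratory mediation analysis, and say that it does not replace those effect sizes.

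In the section on process outcome measures, replace the confounding wording with a comparison of exacerbation frequency and severity by arm, reported as an outcome. Keep the description of how exacerbations relate to capsule intake.

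The cost is a few sentences. The diary already collects everything needed, and neither the sample size nor the visits change.
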